# A guided participation nursing intervention to theraupeutic positioning and care (GP_Posit) for mothers of preterm infants: protocol of a pilot randomized controlled trial

**DOI:** 10.1186/s40814-020-00601-5

**Published:** 2020-05-26

**Keywords:** Guided participation, Maternal sensitivity, Neonatal intensive care unit, Neurodevelopment, Preterm

## Abstract

**Background:**

In the NICU, interventions intended to enhance maternal sensitivity are indicated in order to optimize preterm infant development and long-term mother-infant attachment. A novel nursing intervention was developed following a theory-oriented methodology and is based upon the guided participation theory for mothers to participate in their preterm infant’s therapeutic POSITioning and care (GP_Posit). The primary objective of this study is to evaluate the feasibility and acceptability of (i) the study design; and (ii) the experimental GP_Posit nursing intervention during NICU hospitalization. The secondary objective is to estimate the preliminary effects of GP_Posit on maternal and preterm infant outcomes.

**Methods:**

A pilot parallel-group randomized clinical trial (RCT) was designed where mother-preterm infant dyads are being recruited and randomized to a control group (usual care) or experimental group (GP_Posit intervention). Data collection includes feasibility and acceptability data as well as preliminary effects on maternal sensitivity and infant neurodevelopment. Ethical approval from the University Hospital ethical board was obtained in January 2018 (2017–1540).

**Discussion:**

Data collection for this pilot study is expected to end in 2020. Results of this pilot study will inform about the feasibility and acceptability of the study design and GP_Posit intervention, a nursing intervention having the potential to favor maternal sensitivity and infant neurodevelopment in the NICU and guide the elaboration of a large-scale RCT.

**Trial registration:**

clinicaltrial.gov, NCT03677752. Registered 19 September 2018.

## Introduction

### Background and rationale

While in the neonatal intensive care unit (NICU), the preterm infant’s brain requires nurturing, that being responsive and sensitive caregiving, in order to develop optimally [1]. Maternal sensitivity is the primary predictor of long-term mother-infant attachment [2] and less secure attachment has been found in 1 to 3 years of age children born preterm compared to children born at term [3]. An increase in maternal sensitivity also predicts larger gray matter volume and head circumference in a general population of infants [4]. In children born preterm, an increase in maternal sensitivity significantly predicts improved mental development and social-emotional competence [5], more consistent and symmetric cortical thickness across brain hemispheres [6] and improved cognitive performances [7]. However, maternal sensitivity depends upon the mother’s ability to be responsive to their infant’s cues by detecting, interpreting and responding to those adequately [8], as well as the infant’s ability to demonstrate clear cues [9, 10]. According to the Synactive Theory of Development, preterm infants are able to communicate through stress and stability cues [11]. The cues widely vary from one infant to another, and the most recognizable cues for parents are the behavioral cues which include yawning, flaccidity, finger splays, etc. [11]. Yet, preterm infants lack muscle tone and physiological stability to communicate clear and evident cues, which limits their capacity to be active interaction partners with their parents [9, 12]. Thus, interventions intended to enhance maternal sensitivity, in the NICU, are indicated to enhance preterm infant neurodevelopment [10, 13–15], as preterm infants seem to benefit more from their parent’s sensitivity than infants born at term [16]. Following the emotional crisis mothers go through after having given birth prematurely [17], nurses have a central role in guiding mother to develop their sensitivity to their preterm infant’s cues in the NICU through facilitating physical closeness and participation to their infant’s care [12, 17]. In our systematic review [18] we identified 17 RCTs evaluating the effectiveness of parent-infant interventions on parental sensitivity [19–35]. Interventions evaluated in these 17 RCTs were varied but could be subdivided into two main categories being passive or active interventions. Passive interventions were defined as interventions where parents received information by healthcare professionals on different topics including (I) preterm infants’ behavioral stress and stability cues [20, 26, 28, 31], (II) available emotional support in the NICU, (III) communication and preterm infant’s needs [22], and (IV) how to support their preterm infant’s development [26]. Active interventions were defined as interventions where parents participated in an aspect of their infant’s care such as guided interventions where they were guided by an expert while interacting with or participating in their infant’s care [19, 20, 24, 25, 27, 33–35], stimulating their preterm infant’s senses [23, 29, 33], kangaroo mother care [21], and participation in their infant’s general care such as diapering and bathing [30, 32]. Meta-analyses of these interventions compared to standard care showed not statistically significant effect on parental sensitivity with high heterogeneity. However, these results are based on very low to low quality of evidence primarily because of small sample sizes and high heterogeneity showing the need for developing new and novel theory-oriented interventions to improve maternal sensitivity in the NICU [18]. Based on the paucity of good quality RCTs evaluating parent-infant interventions in the NICU, a novel intervention was developed following a theory-oriented methodology [36]. This intervention is based on the theory of guided participation [37] where mothers are guided by a nurse to interact with their preterm infant while participating in their care and therapeutic POSITioning (GP_Posit). Guided participation [38] has been used in many recent interventions that were evaluated in RCTs on the outcome of sensitivity [19, 20, 27, 33–35, 39, 40]. Moreover, positioning the preterm infant is recognised as being a central part of their care while in the NICU intended to improve their motor development [41]. One RCT evaluated the effects of a parental participation to a motor intervention for preterm infants while in the NICU [42]. Compared to standard care, results showed that preterm infants who received the motor intervention from their parents had a significantly better motor performance at term equivalent age [43], but no significant difference was found on the quality of general movements at three months of corrected age [44]. However, qualitative interviews of experimental group parents highlighted that the intervention empowered them to become competent in providing care and enhanced their feeling of attachment to their preterm infant [45]. Thus, the GP_Posit intervention, combining guided participation of mothers to their preterm infant positioning during NICU hospitalization is being pilot-tested following the below-mentioned methods and preliminary effects on maternal sensitivity and preterm infant neurodevelopment are being evaluated.

### Study objectives

#### Primary objective

The primary objective of this study is to evaluate the feasibility and acceptability of (i) the study design; and (ii) the experimental GP_Posit nursing intervention during NICU hospitalization.

#### Secondary objective

The secondary objective is to estimate the preliminary effects of GP_Posit on mothers and preterm infants’ outcomes. The specific question leading this study is : what are the preliminary effects of the GP_Posit intervention, compared to standard care, at the primary endpoint (when preterm infants will have reached 36 weeks of gestational age (WGA)) on:
(Q1) Maternal sensitivity score to their preterm infant’s cues during oral feeding.(Q2) Maternal beliefs about their preterm infant’s needs and their maternal role in the NICU.(Q3) Preterm infant cerebral activity synchrony during eyes-closed electroencephalogram.(Q4) Preterm infant will have better quality of general movements.

## Methods

The methods for this pilot parallel-group RCT is presented as per the Standard Protocol Items: Recommendations for International Trials (SPIRIT) [46]. All elements of the SPIRIT checklist are reported below (also see Supplemental Material S1 for the checklist).

### Trial design

Given the paucity of evidence on intervention of the same nature as GP_Posit on similar outcomes, we chose to conduct a pilot parallel-group randomized controlled trial (RCT). This design was chosen to test the feasibility and acceptability of this complex and novel intervention in order to identify challenges that may arise prior to undertaking a large-scale RCT [47]. This trial is registered in the ClinicalTrials.gov registry (NCT03677752).

### Study setting

This study is conducted in a level III NICU of a mother and child academic hospital which is the largest NICU in Canada with a capacity of 65 newborns, accounting for approximately 129 infants born between 27 and 32 weeks of gestation each year. Moreover, these infants are cared for in single NICU rooms where parental presence is encouraged 24 h and where parents can sleep at bedside. Positioning tools, such as specialized mattresses and rolls, are available for each hospitalized infant but no specific procedure or protocol about this practice is implemented in this NICU.

### Eligibility criteria

Mother-infant dyads are recruited in the GP_Posit trial as per the following criteria. Dyads are eligible to participate if the mother (1) speaks, writes, and reads French and/or English and (2) is 18 years or older, and the preterm infant(s) is/are (3) born between 27^0/7^ and 31^6/7^ WGA, as estimated by the medical team or antenatal ultrasound performed during the first trimester, and (4) expected to be hospitalized a minimum of 4 weeks in the NICU before being transferred in another center or obtaining their discharge. These criteria have been established in order to ensure that the mother-infant dyads will be in the NICU during an acceptable period of time to participate in the intervention if randomized in the experimental group. Moreover, preterm infants born before 27^0/7^ are not included as they only start to show behavioral stress and stability cues around 28 weeks of gestational age [48] and mothers in the experimental group will be guided to detect these behavioral cues.

Dyads are not eligible if the mother (5) uses illicit substances, (6) has an unstable mental health as evaluated by a NICU healthcare professional, such as a social worker or (7) gives her infant for adoption after birth. These conditions (5 and 6) could hamper parental competencies [49, 50]. Dyads will also not be eligible if the preterm infant(s) (8) requires surgery because their health condition might be too precarious to participate in the intervention, (9) has an intraventricular hemorrhage greater than grade II, (10) has a severe genetic condition associated with neurodevelopmental impairment or (11) receives opioids or anti-epileptic drugs because these conditions might affect infants’ behavioral activity.

### Interventions

#### Experimental group: GP_Posit intervention

##### Theory supporting the experimental intervention

Mothers-infant dyads allocated to the experimental group receive the GP_Posit intervention. The intervention is primarily based on the nursing theory of guided participation (GP) [38]. Through the process of GP, the nurses providing the intervention aim to guide mothers through their care-giving practice so that they can develop appropriate parental competencies towards their preterm infant [38]. To do so, the nurses (experts) engage in a reciprocal relationship with the mothers (novices) in activities of care-giving requiring specific competencies [37, 38]. Activities can be any parental activities regarding their infant’s physical, psychological, and physiological needs as well as their infant’s health [38].

##### Experimental intervention content

The registered nurses providing the GP_Posit intervention aim to guide mothers in developing their sensitivity to their infant’s behavioral cues through positioning as a care giving activity. Most importantly, these care giving activities are only the context provided to guide mothers to interact in an appropriate matter with their infant. Consequently, the intervention nurses guide mothers in detecting their infant’s behavioral stress and stability cues throughout their participation in the care giving activities in order to develop their communication skills with their infant and sensitivity to their cues. In GP_Posit, the care giving activities primarily include basic care such as diapering followed by supine, side-lying, and prone positioning. Based on the mother’s abilities and level of confidence, these activities are being introduced by the intervention nurses in a progressive manner, throughout the weekly sessions. When the maturity of the infant allows for it, and if the mothers feel comfortable with previously introduced care giving activities, the intervention nurses will be able to add bottle-feeding or breastfeeding as an additional care-giving activity. To support the guided participation intervention, intervention nurses have access to Web-based modules developed by a multidisciplinary team at the CHU Sainte-Justine that provides written information as well as pictures and videos adapted for parents of preterm infants on various aspects of their development and care [51]. The Web-based modules were previously pilot tested by a coauthor, and results showed that parents were satisfied and that the positioning module was the most liked by parents [52]. In GP_Posit, nurses may refer to these modules when teaching mother behavioral cues and positioning techniques. Intervention nurses also give an informative booklet to experimental group mothers that contains pictures of various stress and stability cues of preterm infants so mothers can refer to it between intervention sessions.

##### Experimental intervention structure

The intervention is being provided by two neonatal registered nurses who have been trained to implement the experimental protocol. However, the same nurse always meets with the same mothers throughout the intervention. The intervention takes place at the infant’s bedside where one intervention nurse meets with the mother face to face. The intervention always takes place once a week, but the day of the week when intervention takes place depends on mother’s availabilities. The sessions start from the first week after birth to the last week before discharge or transfer to another center, or when the infant reaches 35 weeks of gestational age, whichever occurs first. It is planned that these sessions each last 30 to 45 min. During these weekly sessions, intervention nurses are demonstrating and then coaching mothers in performing the care giving activities, while always interpreting the infant’s cues and encouraging communication within the mother-infant dyad. Fathers are invited to be present during the intervention sessions, but their presence was not mandatory to be eligible to participate in the study.

#### Control group: usual care

Mother-infant dyads allocated to the control group receive usual care. In the study NICU, nurses are thought to position the preterm infants in their incubators using specialized mattresses, but parents participating in their infant’s positioning are not a current practice. Parental participation in their infant’s care is also encouraged but it is not part of a structured practice. Finally, for all infants born before 29 WGA and whose health condition has been critical, the NICU’s physiotherapists establish a positioning care plan and meet the parents to inform them about it. Otherwise, infants with plagiocephaly or torticoli are also followed by the NICU’s physiotherapist for special positioning care plans. Because of randomization, it is expected that there will be an equivalent number of infants benefiting from this particular positioning care plan in each group.

### Outcomes and data collection

Data collection starts following enrolment and consent. Data collection is performed by a member of the research team at different end points: before randomization (−*t*_1_), throughout intervention delivery (*t*_1_ through *t*_3_), and after the intervention that being when the infant reaches 36 WGA (*t*_4_).

#### Sociodemographic and clinical data

Before randomization of dyads (−*t*_1_), sociodemographic and clinical data are collected. Maternal sociodemographic data include age, origin, ethnicity, parity, marital status, level of education, prior experience of having a preterm infant or hospitalized child, type of delivery, occupation and support received by healthcare professionals such as a psychologist, social worker, lactation consultant, or psychiatrist. Sociodemographic data regarding preterm infants include sex, gestational age at birth, birth weight, and respiratory support. Clinical data is collected only for preterm infants and includes APGAR score and SNAPPE-II score [53].

#### Feasibility and acceptability outcomes

The primary objective of this study is to assess the feasibility and acceptability of (i) the study design; and (ii) the experimental GP_Posit nursing intervention during NICU hospitalization. The indicators used to evaluate the feasibility of the design are presented in Table 1 and the acceptability of the intervention in Table 2. These indicators are based upon Feeley and colleagues’ recommendations [54, 55]. A logbook where intervention nurses as well as research team members keep record of the feasibility indicators is used throughout the study (−*t*_1_ to *t*_4_). As for the acceptability indicators, mothers of both groups complete a questionnaire with yes/no questions as well as open questions at the end of their participation in the study (*t*_4_).

**Table 1 Tab1:** Indicators of feasibility

Elements	Question	Indicators
**Feasibility of GP_Posit**		
Equipment and material resources	Was a computer or electronic tablet available when needed during the intervention?	Availability of computer or tablet.
	Were positioning tools available when needed during the intervention?	Availability of positioning tools.
	Is it feasible to provide mothers with an information booklet?	Number of mothers to which document was given.
Context	Is it feasible to provide GP_Posit in the individual NICU rooms?	Disruptive events.
Recruitment	Is it feasible to reach the target population?	Eligible mothers/participating mothers.
Mothers receiving the intervention	Is the intervention appropriate for mothers of preterm infants?	Mother acknowledges that it is acceptable, helpful, and relevant to participate in the intervention.
Content of the interventions	It is feasible to go through the entire planned content of GP_Posit with the mothers?	Content delivered as planned.
	Is all the necessary content already planned in GP_Posit?	Suggestions made by mothers regarding content.
	Is the content of the intervention acceptable for mothers?	Mother’s ratings regarding acceptability of the intervention.
Sequence of the intervention	Is the planned sequence of GP_Posit feasible and adequate?	Respect of the intervention sequence by intervention nurses.
Dose of the intervention	Is the planned dose of GP_Posit feasible?	Respect of the intervention dose by intervention nurses.
	Is the planned dose of GP_Posit appropriate?	Preferences of mothers in terms of the dose delivered.
Mode of intervention	Is guided participation feasible?	Intervention nurses’ opinion regarding feasibility.
	Is the utilization of online modules feasible?	Utilization of online modules as planned.
**Feasibility of the design**		
Recruitment	What is the number of dyads that were recruited compared to the number of dyads that were evaluated for eligibility?	Number of recruited mothers/mothers evaluated for eligibility.
	What are the characteristics of participating dyads?	Sociodemographic data.
	How much time is needed to reach sample size?	Time needed to reach sample size.
Randomization	Is the method of randomization feasible?	Number of non-eligible participants randomized.
Measure methods	Feasible to use EEG to measure neurodevelopment?	Number of EEGs performed.
Data collection	Is it feasible to perform data collection as planned?	% of data collection performed as planned.
Retention	Are we able to retain all dyads throughout the study?	Number of lost to follow-up and reason.
Contamination	Is there a risk of contamination?	% of mothers that were exposed to the content of the intervention.

**Table 2 Tab2:** Indicators of acceptability

Elements	Question	Indicators
**Acceptability of design**		
Recruitment	Do the eligible mothers accept to participate?	% of eligible mothers that participate.
Randomisation	Do the mothers accept to be randomized?	Reason of refusal.
Data collection	Is it acceptable for mothers that we perform EEGs to their preterm infant?	80% of mothers accept.
	Is it acceptable for mothers that we perform the GMA to their preterm infant?	80% of mothers accept.
	Is it acceptable for mothers to be filmed while they breastfeed or bottle-feed?	80% of mothers accept.
	Is it acceptable for mothers to complete questionnaires?	80% of mothers accept.
General acceptability of the intervention^a^	Is it acceptable for mothers to participate in their infant’s positioning?	80% of mothers find it acceptable.
	Is it acceptable for mothers to participate in 30–45 min. intervention sessions, once to twice per week, throughout the hospitalization?	80% of mothers find it acceptable.
Appreciation^a^	Were mothers satisfied by the intervention?	80% of mothers were satisfied.
	Did mothers find it easy to participate?	80% of mothers found it easy.
	Did mothers find it challenging to participate?	Challenges encountered.
	Did the mothers find the intervention useful?	80% of mothers found it useful.
Retention^a^	Which strategies could enhance retention?	Suggested strategies by mothers.

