**Other elements to consider**		
Contamination^a^	Do intervention mothers share content with other mothers?	Number of intervention mothers who shared content.
Co-intervention	Do mothers and/or infant participate in other research projects?	Number of mothers/infants participating in other research projects.

^a^Only for experimental group mothers

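### The 80% acceptability item in Table 2 names one to two sessions a week, but the intervention is fixed at one

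*Protocol article*

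**What the plan says.** The protocol article gives a session frequency in three sections.

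- **Experimental intervention structure:** "The intervention always takes place once a week". Only the day of the week varies, with the mother's availability. Sessions stop at discharge, at transfer, "or when the infant reaches 35 weeks of gestational age, whichever occurs first". On length: "It is planned that these sessions each last 30 to 45 min".
- **Experimental intervention content:** care activities are introduced step by step "throughout the weekly sessions".
- **Table 2, General acceptability of the intervention:** mothers are asked whether they accept 30–45 min "intervention sessions, once to twice per week, throughout the hospitalization". The indicator is that 80% find it acceptable. The row's footnote reads "Only for experimental group mothers".

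Under Feasibility and acceptability outcomes, mothers "complete a questionnaire with yes/no questions as well as open questions" at the end of their participation. Table 1 also lists, under dose, "Preferences of mothers in terms of the dose delivered", with no threshold and no frequency.

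**The concern.** Acceptability of the intervention is part of the primary objective, and this is the only 80% mark in the article that names a session frequency. A dose fixed at one session a week and a criterion written for one to two do not describe the same intervention.

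If mothers are asked the question in the Table 2 wording, two misreadings are possible. A mother content with her weekly session may answer no because she would not want two. A mother who answers yes is counted as accepting a frequency that she was not planned to receive. In either case the percentage does not refer cleanly to the dose being piloted, which is the dose a large-scale trial would carry forward.

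**Working it through.** The article states no figure that can be reproduced here, so the check compares the texts and then sizes the gap.

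**1. Is a second weekly session planned anywhere?**

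| Place in the protocol article | Frequency given |
|---|---|
| Experimental intervention structure | one per week, fixed |
| Experimental intervention content | weekly |
| Table 2, General acceptability of the intervention | one to two per week |
| Table 1, Dose of the intervention | refers to the planned dose, no number |
| Participant timeline | none |
| Feasibility criteria | none (minimum of four sessions in total) |
| Protocol amendments | not mentioned; the two changes are sample size and gestational-age range |

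Only Table 2 mentions a second session. All of this is current text, and no reported amendment explains the difference.

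**2. Which parts of the item agree with the plan?** The 30–45 min length agrees. The lower end of the frequency range agrees. The time span fits infants discharged or transferred before 35 weeks. It is loose only for infants still in the unit after 35 weeks, when sessions have stopped. Participant timeline allows for such infants, since it covers those not yet fully feeding by mouth at 36 weeks.

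**3. Size of the dose gap.** Take an infant born at 27 0/7 weeks, the earliest eligible, who stays until 35 weeks.

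- Weekly: 35 − 27 = 8 sessions, or 35 − 28 = 7 if the first is at 28 0/7, the start that Protocol amendments describes for these infants. Contact time runs from 7 × 30 min = 3.5 h to 8 × 45 min = 6 h.
- Twice weekly: 14 to 16 sessions, from 14 × 30 min = 7 h to 16 × 45 min = 12 h.

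This infant gives the largest totals. Those born later have fewer weeks, but the ratio of 2 to 1 is the same.

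**4. What the 80% mark means in mothers.** The item applies to the experimental arm only.

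| Experimental mothers answering | Needed for 80% | One fewer |
|---|---|---|
| 10 (planned) | 8 (80%) | 7/10 = 70%, fails |
| 9 | 8 (88.9%) | 7/9 = 77.8%, fails |
| 12 | 10 (83.3%) | 9/12 = 75%, fails |

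The row for 9 comes from the maximum of 24 dyads: 24/2 = 12 per arm, and the anticipated 20% attrition leaves 12 × 0.8 = 9.6, so 9 or 10 answer. The row for 12 requires no loss in this arm and is the less likely case, because the extra dyads are there to cover attrition.

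If acceptance of the weekly dose sits exactly at the cut-off, a single no prompted by the twice-weekly wording takes the item below 80%. That sensitivity is shared by every 80% item at this sample size. The article gives no basis for how often such a no would occur, so no acceptance rate is assumed.

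**The case against.** The strongest reply is that the mismatch does little harm. The range includes the planned dose, and the intervention sections agree with each other, so nobody is in doubt about what is delivered. Table 2 lists the researchers' indicators. The questionnaire is not shown and may be worded differently. Mothers answer after a course of weekly sessions, have open questions in which to explain, and are asked about dose preferences under Table 1. The article attaches no stop or go decision to this item and analyses acceptability descriptively. Its primary feasibility criterion is attendance at four or more sessions.

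Most of this stands, and it limits the weight of the point. The effect on answers is conditional on the unseen questionnaire, and the cut-off arithmetic is not specific to this item. It does not remove the contradiction, because overlap at the lower end does not make the upper end planned. Table 1 cannot settle it either, since it names a planned dose without stating it.

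The four-session criterion is untouched only if weekly is the correct text. Four sessions take four weeks at one a week but two weeks at two a week.

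**Conclusion.** The concern holds as a minor inconsistency. One thresholded acceptability item under the primary objective names a frequency whose upper end is twice the planned dose, and nothing in the article plans or explains that upper end. The mismatch in the text is certain. Any distortion of the result depends on the questionnaire repeating the Table 2 wording, and its size cannot be estimated from the article. No effect on the preliminary effect estimates is shown. The four-session criterion is also unaffected, provided that weekly sessions are what is intended.

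**What to change.** Confirm which frequency is intended.

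- If weekly is right, reword the Table 2 item to ask about 30–45 min sessions held once a week until discharge, transfer or 35 weeks of gestational age, whichever is first. Keep the 80% mark.
- If a second session was intended, correct the two intervention sections instead.

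Check the mothers' questionnaire. If it uses the Table 2 wording, align it and identify in the report the answers given to the old wording. With about 10 respondents, a plain count is enough. If the large trial might use two sessions a week, ask about that in a separate item with no threshold.

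The cost is one line in Table 2 and possibly one line in the questionnaire. Design, sample size and thresholds do not change.
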